### Randomisation

Once informed consent has been obtained and baseline measurements have been taken, patients will be randomised blindly and centrally to either the EG or PVS group, stratified by illness type, at the coordinating centre, the Primary care Research Unit of Bizkaia of the Biocruces Bizkaia Health Research Institute. The randomization will be performed using computer-generated random numbers in a 1:1 ratio, stratified by illness type, with a block size of 4 or 6. (Fig. 1).

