### Statistical analysis

The statistical analysis will be performed on an intention-to-treat basis, comparing changes observed from baseline throughout the year of follow-up in participants assigned the EG and PVS group, adjusting for baseline, using mixed-effect analysis of covariance (linear for continuous outcomes and logistic for dichotomous outcomes). The effect of time on the repeated measures in each participant will be estimated and the hypothesis of significantly different (*p* < 0.05) changes in the EG and PVS group will be tested, assessing a treatment group-time interaction term. These models will include an additional effect characteristic of each group and the interaction between the conditions and the effect of the intervention (GE/PVS). The comparisons will be adjusted for potential confounders. The aforementioned effects will be considered fixed and patients and primary care centres will be included as random effects in the intercept, time slope and effect of the programme. Models will be simplified with backward and forward selection using Likelihood ratio tests (selection criteria, *p* < 0.05). A sensitivity analysis will be performed including/excluding outliers. Based on these models, the effect attributable to the intervention will be estimated, calculating the mean differences between groups estimated at each of the follow-up points (adjusted odds ratios for dichotomous outcome variables) and 95% confidence intervals. Before such analysis, potential interaction effects between the specific illness group of the participant and the effect of the interaction would have been ruled out. Regarding missing values, these longitudinal mixed effect models are one of the best approaches for managing missing data. Analysis will be performed by pre-established groups to test hypotheses that the programme is more effective in patients with mental illness, young people, males, those with a high socioeconomic status, less advanced stages of illness and those with certain comorbidities, evaluating an interaction term between these covariates and the intervention (*p* < 0.005). An analysis will also be carried out by protocol, considering the actual dose of physical activity to which each participant has been exposed. Finally, the cost-effectiveness and incremental cost-utility ratios and their confidence intervals will be estimated using resampling techniques (bootstrapping) and a sensitivity analysis will be performed, changing the assumptions of the analysis. The statistical analysis will be performed with SAS and R packages. No imputation method will be used to handle missing data since longitudinal mixed models based on maximum likelihood estimation are more appropriate to deal with missing data [42] than common imputation methods such as last observation carried forward, complete case analysis or other possible forms of imputation.

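### Stepwise selection at p < 0.05 acts on the treatment-effect model with no term protected, so the 12-month confidence interval can fall well short of 95% coverage if group-by-time is dropped

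*Protocol article*

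**What the plan says.** All of this is in the Statistical analysis section of the protocol article unless noted.

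- The hypothesis of different change in the two groups is tested by "assessing a treatment group-time interaction term" at p < 0.05.
- The model also contains "the interaction between the conditions and the effect of the intervention (GE/PVS", and "The comparisons will be adjusted for potential confounders".
- On random effects: "patients and primary care centres will be included as random effects in the intercept, time slope and effect of the programme".
- Then: "Models will be simplified with backward and forward selection using Likelihood ratio tests", with p < 0.05 as the criterion. No term is named as exempt.
- Next: "Based on these models, the effect attributable to the intervention will be estimated, calculating the mean differences between groups estimated at each of the follow-up". Each visit's difference is to carry a 95% confidence interval.
- Immediately after, the section says that, before this analysis, "potential interaction effects between the specific illness group of the participant and the effect of the interaction would have been ruled out".

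The Randomisation section allocates patients 1:1, "stratified by illness type, with a block size of 4 or 6". Study design describes two parallel groups, so each patient receives one programme only.

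**The concern.** The selection rule stands between the full intention-to-treat model and the reported treatment effect. Nothing confines it to nuisance terms or to the predictive model in the second clinical objective.

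The term that matters most is group-by-time. If it stays, the model gives a separate difference at 3, 6 and 12 months. If it goes, the model gives one common difference for all three visits, which conflicts with the growing effect assumed under Sample size. The interval is then computed as though the chosen form had been fixed in advance.

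The illness-by-intervention term has a related problem. It is listed as part of the model and is also to be ruled out beforehand. Whether the trial reports one common effect, which is its declared aim, therefore depends on a test on the same data.

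The random-effects sentence raises a separate question: can a patient-level programme effect be separated from the patient intercept when no patient receives both programmes?

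**Working it through.** **Inputs (Sample size section).** 370 patients with 30% loss leaves 259, about 129 per arm. SD is 40 s, within-patient correlation 0.6, alpha 0.05, and the planned effect 6/12/24 s at 3/6/12 months (2 s per month). Assumed: two-sided alpha, complete visits, normal data, equal correlation between all visits, and baseline adjustment.

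**Variances after baseline adjustment.** Visit variance = 1600 × (1 − 0.36) = 1024. Covariance between visits = 1600 × (0.6 − 0.36) = 384. Residual within-patient variance = 1024 − 384 = 640.

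Visit times 3, 6 and 12 have mean 7 and sum of squares 16 + 1 + 25 = 42.
- SE of the slope difference = √(640/42 × 2/129) = 0.486 s per month.
- SE of the average difference = √((640/3 + 384) × 2/129) = 3.04 s.
- These two estimates are independent under this covariance.

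**The protocol's own figure.** z = 2/0.486 = 4.11 and power = Φ(4.11 − 1.96) = 98.4%. The stated power of over 90% is reproduced for the group-by-time test.

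**Coverage at 12 months if group-by-time is dropped when p ≥ 0.05.** For a true 3/6/12 s effect:
- P(kept) = Φ(1/0.486 − 1.96) = 0.54.
- When dropped, the model reports the average, (3 + 6 + 12)/3 = 7 s, against a true 12 s. The interval half-width is 1.96 × 3.04 = 5.96 s, so coverage is Φ((5.96 + 5)/3.04) − Φ((−5.96 + 5)/3.04) = 0.62.
- When kept, the mean 12-month estimate is 13.8 s and coverage is 0.95 (by simulation).
- Overall: 0.46 × 0.62 + 0.54 × 0.95 = 0.80.

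The same calculation by simulation for other effects:

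| True effect at 3/6/12 months | Group-by-time kept | Coverage with selection | Coverage, fixed model |
|---|---|---|---|
| 0/0/0 s | 5% | 94% | 95% |
| 1.5/3/6 s | 18% | 87% | 95% |
| 3/6/12 s | 54% | 80% | 95% |
| 4/8/16 s | 78% | 84% | 95% |
| 6/12/24 s (planned) | 98% | 94% | 95% |

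**False positives.** Suppose there is no effect and the group main effect is read whenever group-by-time is dropped. Two independent tests give 1 − 0.95² = 9.75%. Simulation with estimated variances gave 9.5% to 10.2% across assumed random-slope SDs of 0 to 3 s per month, and 9.6% with no random slope.

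**Selecting other terms.** With group always kept and 12 candidate baseline covariates open to selection, type I error was 5.2% to 5.7%, against about 5.1% in the full model. Selecting only the random slope gave 5.0% to 5.5%.

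**Patient-level programme effect.** Let the patient intercept have variance a, the programme effect variance b, and their covariance c. Between-patient variance is a in the PVS arm and a + 2c + b in the exercise arm. With the residual variance there are four parameters and three identifiable quantities; the information matrix has rank 3 of 4. Setting c = 0 gives rank 3 of 3, but b is then only the excess between-patient variance in the exercise arm.

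**The case against.** The strongest reply is that the section names group-by-time as the hypothesis test and asks for differences at each visit. Both suggest that this term was meant to stay and that simplification was aimed at confounders and random effects. On that reading the harm is small, as the covariate and random-slope results show. A list of protected terms could also sit in an analysis plan that is not shown. This is a fair reading of intent, but the text does not state it: the rule covers the models without exception, and an analysis plan that protected these terms would have to narrow it.

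Several stronger readings are tempting and are not supported.

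- A reader might infer that all reported p-values and intervals are invalid. Coverage is about 94% at the planned effect and under no effect, and selection of nuisance terms leaves type I error near 5%.
- A reader might count three treatment terms and quote 1 − 0.95³ = 14% as the error rate. That is an independence approximation to the chance of retaining any of them. The protocol names one hypothesis test, and an illness interaction is not a claim of efficacy.
- A reader might infer that the model cannot be fitted and that this undermines the fixed effects. The protocol gives no covariance structure, a diagonal form is estimable, and a centre-level programme effect is estimable where centres hold both arms. An over-parameterised term would more likely fail to converge or be dropped than bias the comparison.
- Dropping illness type has not been shown to cause harm here. It would be dropped only if it predicted little, and omitting a stratification factor usually makes a linear analysis conservative. Keeping it is sound practice rather than the cure for a demonstrated error.

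**Conclusion.** The point holds in this limited form. As written, the selection rule may remove group-by-time from the model that supplies the treatment effect, and the intervals are not adjusted for that. The damage is concentrated at effects of about half to two-thirds of those planned, where 12-month coverage falls to 80–84% instead of 95%. At 3/6/12 s, the mean reported 12-month difference is 7.0 s or 13.8 s according to whether the term is dropped or kept. The 9.6% false-positive rate is conditional on reading the main effect in place of the named test.

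The random-effects sentence needs correcting as a matter of specification. It is not a cause of invalid p-values.

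The figures rest on the Sample size inputs and the assumptions listed in the working. The size of the shortfall would change with other covariance patterns or incomplete visits.

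**What to change.** 1. State one primary model whose terms are kept regardless of p-value: baseline value, illness type, visit, group, group-by-visit, and a covariate list fixed in advance.
2. Name the group-by-visit contrast to be tested. A linear contrast over the visits would match the present hypothesis and the Sample size assumption.
3. Report the illness-by-intervention interaction as a separate, pre-specified test of heterogeneity that does not decide the form of the primary model. Remove the statement that it will have been ruled out first.
4. Limit backward and forward selection to the predictive model of the second clinical objective.
5. Keep a patient random intercept, with a time slope if wanted, and restrict the random programme effect to centres.

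The cost is wording, plus a few non-significant terms retained in a model with about 259 patients. Nominal 95% coverage is restored, and the pre-specified slope test keeps about 98% power at the planned effect, so the stated power of over 90% is unaffected.

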## Methodology

### Study design

This will be a multicentre pragmatic open-label type I hybrid implementation-effectiveness trial, in which a total of 370 patients each with one of 4 different chronic conditions, namely, solid cancer (*n* = 100) and blood cancers (*n* = 70), COPD (n = 100) or schizophrenia (n = 100), will be randomised to one of two parallel groups, stratified by illness type: the EfiKroniK group (EG) (tailored exercise supervised by fitness and health professionals) or the reference group (PVS group) [34]. We deliberately opted to study diverse illnesses seeking to demonstrate any common effect of physical exercise across all of them, independent of any additional effects on each condition separately, and for this purpose, this design is much more efficient than separate clinical trials for each illness. Cardiorespiratory functional capacity at 3, 6 and 12 months and quality of life at baseline and at 6 and 12 months will be considered the primary outcome variables, and we will compare changes over time in both groups. Additionally, we will explore the perceptions of participants and professionals in terms of the feasibility of the programme, as well as the barriers and facilitators for adherence and continuity.

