### Sample size

We expect to recruit a total of 370 patients over 2 years; with a loss to follow-up (including deaths) of 30%, this would provide the study with a power of over 90% to detect differences between the two comparison groups in the primary outcome variable (400-m walk completion time) of at least 6 s after 3 months, 12 s after 6 months and 24 s after 12 months of follow-up as significant (alpha = 0.05), assuming a linear increase in the impact of the exercise over time, a standard deviation of 40 s and intra-patient correlation of 0.6. These differences are less than those found in previous studies.

Regarding the quality of life outcome variable, we would have a power of 90% to detect differences between the two groups of 2.5 points at 3 months, 5 points at 6 months and 10 points at 12 months as significant (alpha = 0.05), for all the dimensions of the SF-36 questionnaire, except for physical and emotional roles (80% power) [40].

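### The main effect estimate is made conditional on having ruled out an illness-by-programme interaction, which this trial is too small to rule out and which the plan itself hypothesises

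*Protocol article*

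**What the plan says.** The Study design section explains that four illnesses were combined "seeking to demonstrate any common effect of physical exercise across all of them", apart from any further effect in each condition. Randomisation is stratified by illness.

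The Statistical analysis section handles the illness-by-programme interaction in several places:

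- The mixed models contain "the interaction between the conditions and the effect of the intervention (GE/PVS"), and models are then simplified by likelihood ratio selection at p < 0.05.
- After describing how the between-group differences will be estimated, it adds: "Before such analysis, potential interaction effects between the specific illness group of the participant and the effect of the interaction would have been ruled out". The last mention of interaction is presumably a slip for intervention. No criterion or margin is attached.
- Pre-established subgroup analyses will "test hypotheses that the programme is more effective in patients with mental illness, young people, males" and others, each judged by an interaction term at p < 0.005. Schizophrenia and related psychoses form the only mental-illness stratum.

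The Clinical objectives also list the moderating role of each illness as something to be assessed. The Sample size section gives power only for the overall two-group comparison.

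**The concern.** Failing to reject equal effects is not evidence that effects are equal. A plan that calls an interaction ruled out on that basis, and then presents a pooled figure as the effect common to four illnesses, can attach that label to a benefit that is much smaller, or absent, in some of them. The common effect is the trial's headline objective, so the interpretation of the main result is at stake.

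The precondition also sits badly with the rest of the plan. The plan expects the programme to work better in mental illness, and mental illness against the rest is a single contrast within the illness interaction. The main estimate is therefore to be made only after excluding something the plan sets out to demonstrate.

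**Working it through.** **Inputs.** Study design: "solid cancer (*n* = 100) and blood cancers (*n* = 70), COPD (n = 100) or schizophrenia (n = 100"). Sample size: "We expect to recruit a total of 370 patients over 2 years", "with a loss to follow-up (including deaths) of 30" per cent, SD 40 s, within-patient correlation 0.6, planned differences of 6, 12 and 24 s at 3, 6 and 12 months, alpha 0.05. Randomisation: 1:1 within illness. Assumed here: two-sided testing, the same 30% loss in every illness, a common SD. The evaluable numbers are then 70 / 49 / 70 / 70 (solid cancer / blood cancer / COPD / schizophrenia), 259 in all.

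**SD range.** Raw 12-month value: 40 s. Baseline-adjusted (ANCOVA): 40 × √(1 − 0.6²) = 32 s. Results are given for 32 and then 40 s.

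**The plan's own figure.** The article states a "power of over 90% to detect differences between the two comparison groups in the primary outcome variable". With variance 4·SD²/n, the SE of the overall 12-month difference is √(4 × 32²/259) = 3.98 s or √(4 × 40²/259) = 4.97 s. For 24 s, power is above 99.9% or 99.8%, so the claim reproduces at 12 months. The overall comparison is not the difficulty.

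**Precision within an illness.** SE = 2·SD/√n: 7.6 or 9.6 s with 70 patients; 9.1 or 11.4 s with 49.

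**Schizophrenia minus the other three.** SE = 2·SD × √(1/70 + 1/189):

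- SD 32: 64 × 0.1399 = 8.95 s; half-width 1.96 × 8.95 = 17.6 s (73% of 24 s)
- SD 40: 80 × 0.1399 = 11.19 s; half-width 1.96 × 11.19 = 21.9 s (91% of 24 s)

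Even an observed difference of exactly zero would leave a true difference of 18 to 22 s inside the interval. This result needs no assumption about the size of the interaction.

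**Illustrative power of a 3-df test at 0.05.** The article states neither the test nor the threshold for this step, so both are assumed. Non-centrality = Σ n(d − d̄)²/(4·SD²), where d̄ is the n-weighted mean effect; power comes from the non-central chi-square distribution (critical value 7.81).

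| True 12-month effects, s (solid / blood / COPD / schizophrenia) | d̄ | Σ n(d − d̄)² | Non-centrality, SD 32 / 40 | Power, SD 32 / 40 |
|---|---|---|---|---|
| 12 / 12 / 24 / 24 | 18.5 | 9,263 | 2.26 / 1.45 | 21% / 15% |
| 0 / 0 / 24 / 24 | 13.0 | 37,051 | 9.05 / 5.79 | 71% / 50% |
| 0 / 24 / 24 / 48 | 24.0 | 80,640 | 19.69 / 12.60 | 97% / 86% |

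Halving the effect in both cancers would usually go undetected. A complete absence of effect in both cancers would be missed in 29% to 50% of trials. Only a very wide spread is found reliably.

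**The zone between the two thresholds.** For the mental-illness contrast, p = 0.05 corresponds to an observed difference of 1.96 × SE and p = 0.005 to 2.81 × SE: 17.6 to 25.1 s at SD 32, 21.9 to 31.4 s at SD 40. In that zone model selection at p < 0.05 would keep the term, while the subgroup rule would not count it as an effect. The article does not say what then follows for the common-effect estimate. Both ranges contain the planned 24 s.

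**The case against.** A fair defence has four parts.

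1. **The wording describes one procedure.** The interaction enters the model, is tested, is dropped if non-significant, and effects are then estimated. On that reading selection at p < 0.05 and the ruling-out step are the same thing, and p < 0.005 is a multiplicity guard for a separate list of subgroups. This stands: a reader might infer three conflicting rules, but the text does not establish that. What remains is the narrow overlap for mental illness.
2. **A significant interaction does not leave the trial without an analysis.** The model that retains the term gives illness-specific effects. This also stands. A reader might infer that the primary analysis is lost in 5% of trials when effects are equal, but that needs a 0.05 gate the article does not state, and it ignores those estimates.
3. **The power figures depend on chosen scenarios.** True: the documents give no interaction size, and the last row of the table shows good power for an extreme spread. The confidence interval width does not depend on the scenario.
4. **The aim is coherent.** Study design looks for a shared component and allows for illness-specific additions. That is correct, and it is why the precondition is unnecessary: an average effect across strata can be estimated whether or not effects differ.

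A reader might also infer that heavier losses in stage IV cancer would weaken the schizophrenia contrast. With total loss fixed at 30%, they would leave more schizophrenia patients and make that contrast slightly more precise.

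**Conclusion.** The concern holds in a limited form. The article makes the absence of an illness-by-programme interaction a precondition of its main estimate, while hypothesising such an interaction for mental illness and making moderation by illness an objective. The trial cannot meet the precondition by a non-significant test: the 12-month interval for schizophrenia against the rest extends about 18 s (SD 32 s) to 22 s (SD 40 s) either side of its estimate, compared with a planned effect of 24 s. This rests on the article's stratum sizes, SD and correlation, and on equal 30% loss, a common SD and two-sided intervals. The 15–21% and 50–71% power figures are illustrations that also assume a 3-df test at 0.05 and the stated effect patterns. The overall comparison remains well powered; what is unsound is the route from it to a claim of one common effect.

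**What to change.** In the Statistical analysis section:

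- Delete the sentence that requires illness interactions to have been ruled out.
- Define the main result as the illness-stratified average programme effect, with illness type as a fixed factor, reported whatever the interaction test shows.
- Keep the illness-by-programme term out of the p < 0.05 stepwise selection.
- Report beside the average the four illness-specific effects with 95% confidence intervals and the interaction test. A partially pooled estimate is optional.
- Describe the effect as common only as far as those intervals support it.

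This needs no further patients, visits or data. It costs a change of wording, one extra table, and a more cautious conclusion: an average effect with its heterogeneity shown.

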## Clinical objectives

The objectives are:

To estimate the common effect of the innovative EfiKroniK programme of physical exercise, supervised by fitness and health professionals, across people with various different chronic conditions (solid or blood cancer, COPD or schizophrenia), compared to that of a general intervention promoting healthy habits (physical activity, balanced diet and smoking cessation). The effectiveness will be explored in terms of:
Cardiorespiratory functional capacity estimated using a 400-m walk testQuality of life and utility, measured using generic and specific questionnaires for each conditionSymptoms, and psychological and social well-being.

*All of these variables will be assessed on recruitment and at 3, 6 and 12 months of follow-up.

We will also measure specific blood parameters at baseline and 3 months (adiponectin, C-reactive protein, TNF-α, Il-1, Il-6, brain-derived neurotrophic factor [BDNF]).

To assess the dose-response relationship between exercise performed and the aforementioned response variables, as well as the predictive, moderating and mediating role of each illness, its treatment and patient characteristics, to build a predictive model of the clinical outcomes of the programme based on these clinical variables.

To estimate the associated costs for the EfiKroniK group and the standard healthy lifestyle prescription (hereon PVS, from the Spanish “*Prescribe Vida Saludable*” meaning prescribing a healthy lifestyle) group and calculate incremental cost-effectiveness and cost-utility ratios.

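### The article plans to express economic uncertainty as bootstrap intervals on ratios, which would be uninterpretable for the cost-utility ratio if the QALY gain proves small; net benefit from the same replicates would remain readable

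*Protocol article*

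**What the plan says.** The Clinical objectives section sets out to estimate costs in both groups and "calculate incremental cost-effectiveness and cost-utility ratios". The Statistical analysis section states how: "the cost-effectiveness and incremental cost-utility ratios and their confidence intervals will be estimated using resampling techniques (bootstrapping"), after which "a sensitivity analysis will be performed, changing the assumptions of the analysis". The Discussion adds that the economic results are meant to show whether such a programme is feasible in healthcare services.

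The article does not mention net benefit, a cost-effectiveness plane, an acceptability curve, a willingness-to-pay value, or how replicates with a zero or negative effect difference are to be treated. Utility appears as an outcome in the objectives, but no utility or QALY difference, standard deviation or cost figure is given anywhere. The Sample size section sizes only walk time and SF-36.

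**The concern.** A ratio is discontinuous where its denominator passes through zero. If the replicates fall on both sides of zero effect, those with a small positive effect give very large ratios of one sign and those with a small negative effect give very large ratios of the other. The sign then no longer tells the reader which conclusion applies. A negative ratio arises when the programme is cheaper and better and also when it is dearer and worse. A positive ratio likewise pools dearer and better with cheaper and worse. An interval formed by ranking these values does not run from favourable to unfavourable.

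Cost-effectiveness is a stated objective and feeds the case for adoption. A ratio interval that is wide, or that spans both signs, for this reason would tell a decision maker little, although the underlying replicates contain a clear answer. The planned sensitivity analysis does not help: it varies assumptions, whereas the difficulty lies in the quantity being summarised.

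**Working it through.** **Inputs from the article.** "We expect to recruit a total of 370 patients over 2 years"; "with a loss to follow-up (including deaths) of 30"%; allocation by "computer-generated random numbers in a 1:1 ratio, stratified by illness type, with a block size of 4 or 6"; design differences of "at least 6 s after 3 months, 12 s after 6 months and 24 s after 12 months of follow-up"; "a standard deviation of 40 s and intra-patient correlation of 0.6"; alpha 0.05, taken as two-sided. Evaluable patients: 370 × 0.70 = 259, or 129.5 per arm.

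**The article's own figure.** It states no economic figure. Its power claim for walk time is over 90%. At 12 months, SE = 40 × √(4/259) = 40 × 0.1243 = 4.97 s; 24/4.97 = 4.83; power = Φ(4.83 − 1.96) = 0.998. The claim is reproduced for the 12-month comparison, so the inputs are being read correctly.

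**Share of replicates at or below zero.** If the effect estimate equals its true value d, this share is about Φ(−d/SE).

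- Walk time, improvement counted as positive: 24 s gives Φ(−4.83), under 0.0001%; 12 s gives Φ(−2.41) = 0.8%; 6 s gives Φ(−1.21) = 11%.
- SF-36, 10 points, if the stated 90% power is taken to apply to that difference: d/SE = 1.960 + 1.282 = 3.24, giving 0.06%. For the two role dimensions at 80% power: 1.960 + 0.842 = 2.80, giving 0.25%.
- QALYs: every input is assumed. With standard deviation 0.15, SE = 0.15 × 0.1243 = 0.0186. Other standard deviations are shown for range:

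| True QALY gain | SD 0.10 | SD 0.15 | SD 0.20 | SD 0.25 |
|---|---|---|---|---|
| 0.01 | 21% | 30% | 34% | 37% |
| 0.02 | 5.4% | 14% | 21% | 26% |
| 0.03 | 0.8% | 5.4% | 11% | 17% |
| 0.04 | 0.06% | 1.6% | 5.4% | 9.9% |
| 0.05 | <0.01% | 0.4% | 2.2% | 5.4% |

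**What gains are plausible?** The article does not say. Its sample size assumes that the effect grows linearly to 12 months. If utility did the same, and QALYs are the area under the utility curve (the usual definition, not stated in the article), the one-year gain would be half the 12-month utility difference. A gain of 0.02 would then correspond to a 12-month difference of 0.04.

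**Effect on the interval.** Assume a gain of 0.02, QALY SD 0.15, extra cost 500, cost SD 3,000, independent costs and effects, and plain percentile limits.

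- SE of cost = 3,000 × 0.1243 = 373, so P(cost difference < 0) = Φ(−500/373) = 9.0%.
- Cheaper and better: 0.090 × 0.858 = 7.7%. Dearer and worse: 0.910 × 0.142 = 12.9%. Both give negative ratios.
- The simulated 95% percentile interval for the ratio is roughly −235,000 to +280,000 per QALY.
- Net benefit at 30,000 per QALY: mean 30,000 × 0.02 − 500 = 100; SE = √((30,000 × 0.01864)² + 373²) = √(559² + 373²) = 672; interval 100 ± 1.96 × 672, about −1,220 to +1,420.
- With the other inputs unchanged, a gain of 0.05 gives a ratio interval of about −5,600 to +45,000, and 0.08 about −3,000 to +19,000. At those gains almost all replicates have a positive effect, so a negative limit simply means lower cost.

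**Coverage.** A second simulation used other assumed inputs: QALY SD 0.2, extra cost 600, cost SD 2,000, threshold 25,000, 129 per arm. At a gain of 0.001 the percentile ratio interval covered the true ratio in 4% of trials, against 93% for net benefit. At gains from 0.01 to 0.10 the ratio interval covered in 93% to 98%. At 0.01, however, it spanned both signs in 96% of trials, with median limits of about −243,000 and +252,000. Outside the near-null case, the failure is therefore one of interpretation more than of coverage.

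**The case against.** The strongest reply has four parts.

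1. **The article's own design effects avoid the problem.** At 24 s or 10 SF-36 points almost no replicate crosses zero, and a ratio interval per second or per point gained would be ordinary. This stands. A reader might infer that every ratio interval in the plan is uninterpretable and should be removed; the documents do not support that.
2. **The QALY and cost figures are assumptions.** This also stands, and the problem fades by a gain of about 0.05 if the standard deviation is 0.15. The article gives no ground for asserting that the gain will be small, and equally none for assuming it will be large. An interval should remain readable when the effect is smaller than hoped.
3. **The bootstrap interval method is not stated.** The article does not commit to plain percentile limits, so the ratio limits above illustrate that one method only. The pooling of opposite conclusions under one sign, however, belongs to the ratio itself.
4. **A journal article condenses, and a fuller economic plan may add net benefit or an acceptability curve.** That may be so, and the lack of a willingness-to-pay value is not in itself a fault here. But the ratio interval is a method the article states, and it would still need to be qualified.

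**Conclusion.** The point holds conditionally, and mainly for the cost-utility ratio. With 259 evaluable patients and an assumed QALY standard deviation of 0.15, about 30%, 14%, 5%, 1.6% and 0.4% of replicates fall at or below zero for gains of 0.01, 0.02, 0.03, 0.04 and 0.05. At the lower gains an interval on the ratio would mix opposite conclusions; at 0.05 and above it would be close to usable. The result depends on the assumed QALY standard deviation and gain, which the article does not supply, and on 259 as the effective number.

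The objectives ask for the ratios, and bootstrapping is a sound way to obtain uncertainty; it would be wrong to conclude that the economic analysis is invalid. Primary outcomes and sample size are unaffected. This is a minor improvement.

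**What to change.** Keep the cost-effectiveness and cost-utility ratios as point estimates, each reported with incremental cost and incremental effect and their own intervals. From the same bootstrap replicates, make incremental net monetary benefit, with intervals over a willingness-to-pay range stated in advance, the main expression of uncertainty for the cost-utility analysis. Add the cost-effectiveness plane and the acceptability curve. Report an interval for a ratio only when essentially all replicates have a positive effect difference, and fix in advance what share counts as essentially all.

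No new data or resampling are needed. The cost is a change of wording and the need to choose and justify the willingness-to-pay range before the results are seen.
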